**PURPOSE OF THE STUDY AND THE BACKGROUND (1-2).**

**1. Purpose of the Study**

**What are the specific scientific objectives (aims) of the research?**

Primary goals:

1. Compare the safety and efficacy of single-dose (6 mg/kg) rATG induction with the same total dose (6 mg/kg) administered every other day for four doses (divided-dose).
2. Compare standard renal transplantation outcome measures in patients converted approximately 6 months post-transplantation from maintenance immunosuppression with sirolimus and tacrolimus to sirolimus and low-dose mycophenolate mofetil.

Secondary goals:

1. Determine the immunological consequences of single-dose (6 mg/kg) versus divided-dose administration of rATG
2. Determine the immunological consequences of calcineurin-inhibitor (CNI) continuation versus CNI withdrawal.
3. Perform a cost analysis of single-dose vs. divided-dose administration of rATG.

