**METHODS AND PROCEDURES (10-12)**

**10. Methods and Procedures Applied to Human Subjects**

a. Briefly describe the study design (e.g. randomized, double blind, cross-over, phase III).

This is a prospective, randomized, non-blinded 2 x 2 factorial comparison of clinical outcomes in 180 renal transplant recipients receiving either a single dose of rATG at 6 mg/kg or 4 doses given every other day at 1.5 mg/kg/dose. Immediately after renal transplantation, each of these groups will undergo our clinically-standard early steroid withdrawal; approximately 6 months later, half the subjects in each group will be switched to maintenance immunosuppression using Sirolimus/MMF.

**b. Are there any tests performed prior to signing of the consent form in order to determine eligibility for this research protocol?** No.

**c. Describe sequentially all procedures, interventions and evaluations to be applied to subjects, and identify any that are experimental or performed exclusively for research purposes.**

Participants must sign a written consent form prior to initiation of any study procedure.

At the time of transplantation, the participant will be randomized to one of 4 groups: (1) single-dose rATG at 6 mg/kg plus rapamycin and tacrolimus maintenance immunosuppression, (2) divided-dose (4 doses) rATG given every other day at 1.5 mg/kg/dose plus rapamycin and tacrolimus maintenance, (3) single-dose rATG plus rapamycin and tacrolimus maintenance with conversion after 6 months to rapamycin and mycophenolate mofetil maintenance, and (4) divided-dose rATG plus rapamycin and tacrolimus maintenance with conversion after 6 months to rapamycin and mycophenolate mofetil maintenance. Given the long-term effects of rATG, single-dose versus divided-dose administration may have a differential impact on the patient’s requirements for maintenance immunosuppression (see section II.2). For this reason, we are randomizing patients to the 4 treatment groups delineated above.

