Participants will receive all standard post-transplant clinical care and follow-up. This includes receiving both tacrolimus and rapamycin for the first 6 months post-transplantation. At the month 6 time point, the investigator will determine if it is safe for those subjects in groups 3 and 4 to transition to rapamycin and mycophenolate mofetil for maintenance immunotherapy. Eligible subjects will have had no rejection episodes in the first six months and will be able to tolerate a dose of rapamycin that achieves a trough level of no less than 8 ng/ml.

Participants will have renal function determined by estimated glomerular filtration rate (GFR) calculated according to the formula currently recommended by the National Kidney Foundation^6,7,8^. These GFR assessments will be made daily during the first one to three weeks post-transplantation, becoming monthly thereafter. 24-hour urine creatinine clearance at 1, 3, 6, 12, and 24 months may also be used to assess graft function. The creatinine clearance test is standard practice. There are a number of factors which can affect the accuracy of the 24 hour urine collection, such as misinterpretation of the instructions provided to patients regarding method of collection; temperatures at which the samples are maintained; and a voiding that is not collected, thus yielding an altered result. The calculated GFR will provide an accepted, objective measure for comparison among the groups.

Participants will undergo assessment of several immunologic parameters to assess potential mechanisms of action of each of these dosing regimens. Each of the parameters will be tested from peripheral blood samples obtained during routine clinical visits.

To measure the long-term effect of rATG, CD3 and CD4/CD8 counts with ratio will be done at baseline, two weeks post transplant, 1, 3, 6, 12, and 18 months, and annually to year 5. These tests are performed for research purposes.

Participants may be asked to have this additional blood drawn in order to test for certain immunological parameters. This will depend on whether or not the patient is able to return to the transplant center at the required intervals. The investigator, in consultation with the patient and the study coordinator, will determine if this is possible.

The following blood tests will be performed to determine if T-cells are being re-educated in the thymus following rATG administration:

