3. PTLD

4. Hyperlipidemia

5. Wound healing problems

6. Lymphoceles

1. Requirement for additional immunosuppression (such as corticosteroids, antimetabolites or other immunosuppressive agents)
2. Acute rejection per kidney biopsy (Banff grading criteria)
3. ATN (acute tubular necrosis) rate (requirement for dialysis within 7 days post-transplant)
4. Graft survival
5. Patient survival
6. Immunological parameters
7. New onset BK virus per kidney biopsy
8. **Describe the follow-up of subjects and identify any procedures that are performed exclusively for research purposes, or performed more frequently than would normally be clinically indicated (e.g. additional or more frequent radiologic evaluations).**

All participants will follow the standard post-transplant schedule for routine laboratory testing.

For safety purposes, subjects will have surveillance biopsies at 6, 12, and 24 months. The renal biopsy at 24 months following transplant is performed exclusively for research purposes. Subjects who present with a condition, either medically or anatomically, that would present a greater risk to the subject, may at the discretion of the Principal Investigator forego a kidney biopsy. It is standard practice at this center to request surveillance biopsies for renal transplant recipients who are not receiving steroids as part of their maintenance immunosuppression.

Participants will return for study visits at 1, 3, 6, 12, and 24 months and as needed in accordance with standard schedule for all transplant patients. Long-term data regarding graft and patient survival, incidence of allograft rejection, serious adverse events, CMV disease, opportunistic infections, PTLD, hyperlipidemia, wound healing problems, lymphoceles and immunosuppression regimen will be collected at years 3, 4, and 5 from a review of the subject’s medical record.

To measure the long-term effect of rATG, CD3 and CD4/CD8 counts with ratio will be done at baseline, two weeks post transplant, 1, 3, 6, 12, and 18 months, and annually to year 5. These tests are performed for research purposes.

Participants may be asked to have this additional blood drawn in order to test for certain immunological parameters. This will depend on whether or not the patient is able to return to the transplant center at the required intervals. The investigator, in consultation with the patient and the study coordinator, will determine if this is possible.

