**e. Describe briefly the statistical methods used to analyze the data.**

Binomial and numerical outcomes are described using proportions and means, respectively, and are compared using chi-square test or Fisher’s exact test when appropriate and t test, respectively. Graft survival and acute rejection rates are determined using Kaplan-Meier estimates and are compared using log-rank tests. The effects of covariates on the hazard risk of graft survival and acute rejection are evaluated using a Cox proportional hazard model.

A mixed-model for repeated measures is used to compare calculated GFR values to examine the effect of single versus divided-dose rATG on kidney function. A linear mixed-model of repeated measures is used to examine the relationship between the amount of rATG infused at the time of reperfusion and calculated GFR during the follow-up period.

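### Under the protocol's general rule the serial CD3 and CD4/CD8 counts would be compared by unadjusted t test, without the baseline value or the repeated-measures structure, which costs precision on a secondary endpoint

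*Protocol*

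**What the plan says.** Item 10.c, repeated in the follow-up part of item 10, schedules the lymphocyte series: "CD3 and CD4/CD8 counts with ratio will be done at baseline, two weeks post transplant, 1, 3, 6, 12, and 18 months", then yearly through year 5. Both places describe these as research tests. Item 10.c also says that extra blood for immunological parameters depends on whether the patient can return to the center, so not every draw is assured.

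The series serves the first secondary goal in item 1, "Determine the immunological consequences of single-dose (6 mg/kg) versus divided-dose administration of rATG", and the second, which asks the same about continuing or withdrawing the calcineurin inhibitor (CNI). In the endpoint list it falls under the secondary endpoint "Immunological parameters".

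Item 10.e gives the methods. Binomial and numerical outcomes "are compared using chi-square test or Fisher’s exact test when appropriate and t test, respectively". The first repeated-measures model is tied to one outcome: "A mixed-model for repeated measures is used to compare calculated GFR values to examine the effect of single versus divided-dose rATG on kidney function". The second, on the amount of rATG infused by reperfusion, also has calculated GFR as its outcome. Covariates appear once: "The effects of covariates on the hazard risk of graft survival and acute rejection are evaluated using a Cox proportional hazard model".

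Item 10.e does not mention the CD counts by name.

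**The concern.** CD3, CD4 and CD8 counts and the CD4:CD8 ratio are numerical outcomes and are not GFR, so the rule that reaches them in 10.e is the t test of means. That test leaves in its error term all variation between patients that existed before rATG. A baseline value is scheduled and could remove part of that variation, but no place in the protocol gives it a role in the comparison, either as a covariate or through a change score.

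The t test also handles one time, or one summary, at a time. With draws that depend on ability to return, t tests at different times would compare different subsets of patients. Unless one time or summary is named, they would give no single answer on the lasting CD4:CD8 change that the background (item 2) stresses. The same section already gives a suitable method to the other numerical outcome that is measured serially.

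At stake is the precision of a mechanistic secondary comparison. The primary endpoints are not affected.

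**Working it through.** **Which method applies (item 10.e).**

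| Outcome | Stated method | Baseline or covariates | Repeated measures |
|---|---|---|---|
| Calculated GFR | Mixed models | Not stated | Yes |
| Graft survival, acute rejection | Kaplan-Meier, log-rank, Cox | Yes, in Cox | Not applicable |
| Other numerical outcomes, so CD3, CD4/CD8 and ratio | t test | None | None |

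**Number of measurements.** After baseline: 2 weeks and 1, 3, 6, 12 and 18 months make 6; years 2, 3, 4 and 5 make 4. The total is 6 + 4 = 10 later times.

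**Power.** The protocol gives no alpha, effect size, SD, power or correlation for this endpoint, so there is no figure of its own to reproduce.

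Inputs:
- Item 10.a plans a "comparison of clinical outcomes in 180 renal transplant recipients". With equal allocation that is 180/2 = 90 per induction arm.
- Assumed: two-sided alpha 0.05, and an effect for which the plain t test has 80% power.
- Assumed: rho, the correlation of follow-up with baseline, from 0 to 0.7.

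The standardised difference with 80% power is d = (1.960 + 0.842) × sqrt(2/90) = 0.418 SD.

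Adjusting for baseline multiplies the residual variance by 1 − rho². Hence

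power = Φ(2.802 / sqrt(1 − rho²) − 1.960).

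At rho 0.5: 2.802/0.866 = 3.235; 3.235 − 1.960 = 1.275; Φ(1.275) = 0.899.

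| rho | Variance removed | Power, adjusted | Patients per arm that match the t test with 90 |
|---|---|---|---|
| 0 | 0% | 80.0% | 90 |
| 0.2 | 4% | 81.6% | 86 |
| 0.3 | 9% | 83.6% | 82 |
| 0.5 | 25% | 89.9% | 68 |
| 0.7 | 51% | 97.5% | 46 |

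The last column is 90 × (1 − rho²). The power column does not depend on the number per arm once the t test is set at 80%; with 81 per arm (90 less 10%) it is the same, with d = 0.440.

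A simulation of 4,000 trials per value of rho agreed. The adjusted analysis had 79%, 81%, 89% and 97% power at rho 0, 0.3, 0.5 and 0.7, and the t test 77% to 79%.

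**Would change from baseline do?** A change score has variance 2(1 − rho) times that of a single value. At the same d its power is 66% at rho 0.3, 80% at 0.5 and 95% at 0.7. It is worse than the plain t test below rho 0.5, so it is not a safe substitute.

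These figures concern one follow-up time. The further gain from modelling the times jointly was not quantified.

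**The case against.** Item 10.e answers a form's request for a brief description. It does not name the CD counts, does not say that a test is run at each visit, and does not say that the baseline is ignored. A SAP could settle all of this. The counts are a secondary, mechanistic endpoint, and an unadjusted t test in randomised arms is valid. Base power and rho are both assumed. The background describes CD4 cells returning largely from the thymus and CD8 cells by peripheral proliferation, which could weaken the link with the pre-rATG ratio even years later.

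Much of this stands. A reader might infer that the protocol has decided on ten separate t tests and to discard the baseline. The text does not support that; it supports only that the stated rule, applied as written, makes no use of either feature. A reader might also infer a biased comparison, or a real power loss of 10 to 17 points. Randomisation rules out the first as a consequence of omitting baseline, and the second rests wholly on the assumed rho. Nor can one say that every subject will have a complete series.

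The objection does not remove the point. Item 10.e is not silent: it states a rule for numerical outcomes and limits the better method to GFR. A SAP that used a baseline-adjusted model here would be departing from that rule, not filling a gap.

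**Conclusion.** The point holds as a modest improvement. Under 10.e as written, the serial CD3, CD4/CD8 and ratio data would be compared by unadjusted t test, without the baseline value or the repeated-measures structure. The consequence is lost precision on a secondary endpoint, not bias.

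The loss ranges from nothing at rho 0, through about 4 points of power at 0.3 and 10 at 0.5, to about 17 at 0.7, all against an assumed 80%. It is probably small in the weeks of depletion. The protocol gives no basis for saying how large it is later.

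The pre-rATG baseline is the natural covariate only for single versus divided dose. For continuing versus withdrawing the CNI, the value just before the regimens diverge is the one at month 6.

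**What to change.** In 10.e, extend the mixed model for repeated measures to log CD3, log CD4, log CD8 and log CD4:CD8 ratio, in place of the t test:

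- **Single versus divided dose:** include the pre-rATG baseline (log scale), randomised induction group, time, and group-by-time. The last term keeps early depletion and late reconstitution from being averaged into one effect.
- **CNI continuation versus withdrawal:** model the values after month 6, with the month 6 value as covariate, by randomised maintenance group whether or not conversion took place.

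The model uses every available measurement, which suits draws that depend on ability to return, although it relies on missed draws being explained by the data in the model. The log scale is a suggestion for counts and ratios and can be checked on the data.

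The cost is slightly more analysis work and a few sentences of text. No new data, visits or subjects are needed.

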- Transglutaminase expression will be measured 1 hr post-initiation of first dose of rATG.

● Serum levels of ε (γ-glutamyl)-lysine diisopeptide will be measured every other day for 7 days post-transplantation then weekly until pre-transplant levels are reached.

● TREC output will be measured weekly, until levels return to baseline, beginning 2 days post-completion of rATG therapy.

● CD3 counts will be measured daily until total counts are > 100.

● Gene array analyses for assessment of functional signal transduction pathways and analysis of cell surface phenotypes of peripheral blood leukocytes will be performed at 1, 3, 6, and 12 months post-transplantation.

All participants will follow the standard post-transplant schedule for routine laboratory testing.

For safety purposes, subjects will have surveillance biopsies at 6, 12, and 24 months. If future funding becomes available, a renal biopsy at year 5 may be added. (If this becomes feasible, the protocol will be amended and an addendum consent form will be prepared for the subjects.) Subjects who present with a condition, either medically or anatomically, that would present a greater risk to the subject, may at the discretion of the Principal Investigator forego a kidney biopsy. Banff scoring will be utilized to categorize rejection and transplant nephropathy. It is standard practice at this center to request surveillance biopsies for renal transplant recipients who are not receiving steroids as part of their maintenance immunosuppression.

Participants will return for study visits at 1, 3, 6, 12, and 24 months and as needed in accordance with standard schedule for all transplant patients. Long-term data regarding graft and patient survival, incidence of allograft rejection, serious adverse events, CMV disease, opportunistic infections, PTLD, hyperlipidemia, wound healing problems, lymphoceles and immunosuppression regimen will be collected at years 3, 4, and 5 from a review of the subject’s medical record.

Adverse Events:

All adverse events will be monitored and recorded. These will include both events related to the safety profile of the study drugs (CMV disease, Post-Transplant Lymphoproliferative Disorder [PTLD], opportunistic infections, elevated lipids, etc.) and expected renal transplant complications (wounds, lymphoceles, diabetes, weight gain, etc.). All unexpected adverse events and any deaths will be reported to the IRB per UNMC policies.

Endpoints:

Primary endpoints:

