**f. Does this research involve genetic testing?**

Genetic testing will not be involved in this research protocol.

**g. Does this research involve banking of information or material (blood, tissue, etc) for future use or for purposes that are not integral to the current research?**

This research involves the collection and storage of data for comparison between enrolled study subjects. This information to be collected and analyzed is data that are currently collected and stored as part of the standard clinical care that a transplant recipient receives. Gathering of this information will continue as long as the graft is functioning or until the subject passes away and may be used in future publications. This project does not involve the banking of blood, tissues, etc.

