**c. What are the specific subject withdrawal criteria?**

Criteria for subject withdrawal from this study include:

- Withdrawal of consent by the subject at any time during the course of the study
- Second transplant after initial kidney transplant (i.e. pancreas and liver)
- Graft loss
- Subject is lost to follow-up
- Pregnancy
- Patient experiences an unmanageable adverse event
- Death of subject
- Study is terminated

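### Patient survival and safety events are to be collected to year 5, but graft loss is a study-withdrawal criterion and follow-up after it is not provided for

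*Protocol*

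**What the plan says.** Four places in Section II of the protocol bear on this.

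- **Endpoint.** The secondary endpoints in item 10 list "Patient survival" separately from graft survival.
- **Long-term data.** Items 10c and 10d both promise "Long-term data regarding graft and patient survival, incidence of allograft rejection, serious adverse events, CMV disease, opportunistic infections", PTLD and further outcomes. The list ends with "immunosuppression regimen will be collected at years 3, 4, and 5 from a review of the" medical record.
- **Withdrawal.** Item 15c opens "Criteria for subject withdrawal from this study include" and includes graft loss. The withdrawal is from the study, not from a drug or a procedure, and no exception is made for vital status.
- **Duration of data gathering.** Item 10g, on stored routine-care data, says: "Gathering of this information will continue as long as the graft is functioning or until the subject passes away".

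On analysis, item 10e says "Graft survival and acute rejection rates are determined using Kaplan-Meier estimates and are compared using log-rank tests". Patient survival is not named there. The same item says "Binomial and numerical outcomes are described using proportions and means, respectively".

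**The concern.** Graft loss happens after randomisation and may be affected by treatment. The abstract hypothesises better graft survival with single-dose rATG. Item 13 tells subjects that one group may carry a higher risk of rejection. If graft loss ends follow-up, the subjects who leave may differ between arms, in number and in kind.

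Read as written, the withdrawal rule turns patient survival into death with a functioning graft. Infections, PTLD and serious adverse events that occur after graft loss, but follow the same immunosuppressive exposure, would drop out too. At stake are a secondary endpoint and the long-term safety comparison, for both factors of the 2 x 2 design.

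**Working it through.** **1. The passages side by side.** Items 10c and 10d set a five-year horizon for patient survival and safety outcomes, with no condition that the graft still functions. Item 15c removes the subject from the study at graft loss. Item 10g gives two end points joined by *or*, so it can be read as stopping at graft failure or as running until death. No sentence says what is collected after graft loss. The protocol states no figure on this point, so there is none to reproduce.

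**2. Illustration.** The protocol gives no rates of graft loss or death, so every rate below is an assumption. Take constant hazards over T = 5 years:

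- death with a functioning graft, d = 0.02 per year in both arms
- death after graft loss, p = 0.08 per year in both arms
- graft loss, g = 0.02 per year in arm A and 0.06 in arm B

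*True mortality* = 1 − [e^(−(g+d)T) + g·(e^(−pT) − e^(−(g+d)T)) / (g+d−p)]; when g+d = p, the second term in the bracket is g·T·e^(−pT).

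- A: 1 − [0.8187 + 0.02 × (0.6703 − 0.8187)/(−0.04)] = 1 − 0.8929 = 10.7%
- B: 1 − [0.6703 + 0.06 × 5 × 0.6703] = 1 − 0.8714 = 12.9%

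*Crude proportion, follow-up ending at graft loss and withdrawn subjects taken as alive* = d/(g+d) × (1 − e^(−(g+d)T)).

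- A: 0.50 × 0.1813 = 9.1%
- B: 0.25 × 0.3297 = 8.2%

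*Kaplan-Meier censored at graft loss* = 1 − e^(−dT) = 1 − e^(−0.1) = 9.5% in both arms.

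| | Arm A | Arm B |
|---|---|---|
| True 5-year mortality | 10.7% | 12.9% |
| Crude, counted to graft loss | 9.1% | 8.2% |
| Kaplan-Meier, censored at graft loss | 9.5% | 9.5% |

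**3. Scale.** With 180 subjects there are about 90 per rATG group. True deaths are 0.107 × 90 = 9.6 and 0.129 × 90 = 11.6, a gap of about two. Counted deaths are 0.091 × 90 = 8.2 and 0.082 × 90 = 7.4, a reversal of less than one death.

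**4. Sensitivity.**

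- With g of 0.02 to 0.06 and p of 0.05 to 0.10, the share of deaths missed runs from 11% to 40%.
- With p of 0.06 to 0.15, true survival in arm B is 1.5 to 4.2 points lower than in arm A. The crude figure still puts arm B 0.8 points higher, because p does not enter that formula.
- With p = d = 0.02 there is no true difference, and censored Kaplan-Meier is correct. The hidden difference therefore depends on excess mortality after graft loss.
- A variant assumes that half the subjects are at higher risk of both graft loss and death, and that graft-loss hazards are three times as high in one arm. True survival is then 88.5% v 85.0%, and censored Kaplan-Meier gives 90.8% v 91.3%. A small reversal can thus appear there too, on these further assumptions.

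**The case against.** The strongest reply is that nothing bars the later data. The item 15c list also contains death, which is plainly recorded, so being on the list does not fix how an outcome is handled. The year 3 to 5 review uses the medical record, needs no visit and is not limited to active subjects. Item 10g mentions continuing until death. Item 10c adds: "All unexpected adverse events and any deaths will be reported to the IRB per UNMC policies". **This stands in part.** A reader might infer that deaths after graft loss are never counted; the text does not go that far. But the IRB sentence is safety reporting and sets up no endpoint follow-up of withdrawn subjects. A survival endpoint should not rest on which reading of who is followed staff adopt.

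Second, the illustration is not anchored in the trial. Graft loss of 2% v 6% per year means about 9% v 25% of subjects by year 5, roughly 8 v 22 of 90. A gap that size would be visible in the separate graft-survival comparison. Item 19b reports no detected difference in patient or graft survival in the first 142 patients. **This stands** as a limit on size. However, that report compares the rATG groups. Item 15e leaves the timing of the calcineurin-inhibitor withdrawal analysis still to be defined.

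Third, the protocol gives no source for higher mortality after graft loss. **This stands**; it is used here only as an assumption.

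Fourth, censoring rules can be left to an analysis plan. **This stands** for the choice of estimator. It does not answer the gap in collection, since an analysis plan cannot recover deaths that were not collected.

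**Conclusion.** The point holds as an internal conflict: outcomes promised to year 5, a withdrawal rule at graft loss with no exception, and an ambiguous statement of how long data are gathered. Follow-up of deaths and safety events after graft loss is not provided for.

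The bias is conditional. It needs withdrawal to be applied as written and graft loss to differ by arm; a hidden true difference also needs higher mortality after graft loss. Under the main assumed rates, a true difference of 10.7% v 12.9% disappears under censored Kaplan-Meier. It reverses, by under one death per 90, in a crude proportion that takes withdrawn subjects as alive. The protocol does not say that patient survival will be analysed in either way.

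A reader might infer that the arm losing more kidneys will look better on survival. The documents do not support that as a prediction, only as a possibility. The primary endpoints, nephropathy and renal function, are outside this point. It should be corrected because it touches a secondary endpoint and long-term safety, and the correction is cheap.

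**What to change.** Reconcile items 10c, 10d, 10g and 15c:

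- In item 15c, state that graft loss ends graft-specific assessments (GFR, biopsy) but not follow-up.
- State that the planned record review at years 3, 4 and 5 for vital status, serious adverse events, infections and PTLD covers every randomised subject who has not withdrawn consent, whether or not the graft functions.
- Reword item 10g to match.
- Report patient survival as all-cause death by randomised group, without censoring at graft loss. This sentence may sit in the protocol or the analysis plan.

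The cost is record follow-up of subjects with graft loss, with no added visit or procedure. Those already enrolled may need a consent addendum: item 29 shows that one was used for the earlier extension of follow-up and the 24-month biopsy. Whether the current consent already allows follow-up after withdrawal cannot be judged from the text at hand.

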1. Cumulative calcineurin nephrotoxicity/ transplant nephropathy per clinically-indicated and protocol surveillance biopsies (Banff grading criteria)
2. Renal function by either measured 24-hour urine creatinine clearance at 1, 3, 6, 12 and 24 months or calculated GFR (Glomerular Filtration Rate) by using the abbreviated MDRD (aMDRD) formula and patient serum creatinine and demographic data. This may be calculated from routine blood draws, allowing multiple data points to be collected within each month.

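### Primary endpoint 1 is a judgement-based biopsy reading in a non-blinded trial, and no masked reading is specified. After month 6, knowledge of tacrolimus exposure could tilt the continuation-versus-withdrawal comparison.

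*Protocol*

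**What the plan says.** Protocol section 10.a gives the design: "This is a prospective, randomized, non-blinded 2 x 2 factorial comparison of clinical outcomes in 180 renal transplant recipients". The first primary endpoint, in section 10.c, is "Cumulative calcineurin nephrotoxicity/ transplant nephropathy per clinically-indicated and protocol surveillance biopsies (Banff grading criteria"). The same section says earlier that "Banff scoring will be utilized to categorize rejection and transplant nephropathy", and gives the schedule: "For safety purposes, subjects will have surveillance biopsies at 6, 12, and 24 months". Clinically indicated biopsies also count toward the endpoint.

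The abstract and section 1 both make continuation versus withdrawal of the calcineurin inhibitor a primary comparison. Tacrolimus exposure differs by design only from month 6. Before that, all groups have the same plan: "This includes receiving both tacrolimus and rapamycin for the first 6 months post-transplantation". Then "approximately 6 months later, half the subjects in each group will be switched to maintenance immunosuppression using Sirolimus/MMF".

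The second primary endpoint is renal function. Section 10.c says of one of its two measures: "The calculated GFR will provide an accepted, objective measure for comparison among the groups". No comparable safeguard is stated for the biopsy endpoint. The protocol names no reader, describes no masked, central or duplicate reading, and gives no histological criterion separating calcineurin nephrotoxicity from other transplant nephropathy.

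**The concern.** Whether a chronic lesion is present, and how it is graded, is partly a matter of judgement. Part of this endpoint's label is also a causal diagnosis that names the drug class under test. A reader who can see that one patient still takes tacrolimus and another stopped at month 6 has a reason to look harder for a lesion, or grade it higher, in the first. With identical tissue in both arms, that would make withdrawal look better on a primary endpoint. Biopsy-graded acute rejection, a secondary endpoint, is read under the same unspecified conditions.

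The reading conditions are trial conduct, so an analysis plan written later could not remove a bias already present in the scores.

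**Working it through.** The documents give no figure to reproduce: no expected nephropathy rate, error level or power appears in the text, and the sample-size analysis is an attachment that is not shown. The steps below establish where the mechanism can act and then illustrate its size.

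**Where it can act**

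- *Biopsies to month 6:* tacrolimus is planned for everyone, so knowing the exposure cannot separate the arms.
- *Biopsies after month 6, including those at 12 and 24 months:* exposure differs between Groups 1 and 2 (continue) and Groups 3 and 4 (convert if eligible).
- *Single versus divided rATG:* tacrolimus is the same to month 6 and balanced by the factorial design afterwards. Only knowledge of the rATG arm itself could matter there, which is a different route.
- *Calculated GFR:* not exposed to a slide reader.

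**Inputs**

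- From the protocol: 180 subjects allocated 1:1:1:1, so 180/2 = 90 per factorial margin.
- Assumed: two-sided 5% test of two proportions, no true difference between arms, and the scoring rates stated below.

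**Formula**

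Let p1 and p2 be the scored rates off and on tacrolimus, d = p2 − p1, p̄ = (p1 + p2)/2, and n the number per margin.

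- SE0 = √[2p̄(1 − p̄)/n]
- SE1 = √{[p1(1 − p1) + p2(1 − p2)]/n}
- False-positive rate = Φ[(d − 1.96·SE0)/SE1] + Φ[(−d − 1.96·SE0)/SE1]

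**Illustration A: lesions missed or scored below threshold**

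Assume lesions in 30% of subjects in both arms, with 5% of them not counted on tacrolimus, so p2 = 0.30 × 0.95 = 0.285.

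| Not counted off tacrolimus | p1 | d | False-positive rate, n = 90 |
|---|---|---|---|
| 10% | 0.30 × 0.90 = 0.270 | 0.015 | 5.6% |
| 20% | 0.30 × 0.80 = 0.240 | 0.045 | 10.5% |
| 40% | 0.30 × 0.60 = 0.180 | 0.105 | 38% |

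Middle row in full: SE0 = 0.0656 and SE1 = 0.0655. The terms are Φ(−1.276) = 0.101 and Φ(−2.650) = 0.004, which sum to 0.105.

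**Illustration B: excess positive readings on tacrolimus**

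The scored rate off tacrolimus is assumed to be 20%, 30% or 40%, with n = 90.

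| Excess d | 20% | 30% | 40% |
|---|---|---|---|
| 5 points | 12.6% | 11.0% | 10.4% |
| 10 points | 34.0% | 28.9% | 27.0% |
| 15 points | 61.7% | 54.8% | 52.2% |

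If 10% of biopsies were unavailable (n = 90 × 0.9 = 81), the 10-point row becomes 31%, 27% and 25%. With no differential, every entry is 5%.

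**The case against.** **Silence is not unmasked reading.** A reader might infer that the slides are read with full knowledge of treatment. The documents do not say so. "Non-blinded" describes the trial design, and nothing is stated about what the pathologist sees. Only the absence of a specified masked reading can be claimed.

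**Relabelling need not move the endpoint.** A reader might infer that calling the same lesion calcineurin toxicity in one arm and something else in the other creates a spurious difference. The endpoint joins the two terms with a slash. If either label counts, which is a natural reading, a relabelled lesion stays in the total. The endpoint shifts only if knowledge of exposure changes whether a lesion is scored at all or how severely. That remains possible, and Illustration A should be read that way.

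**Banff gives structure.** This largely stands. The endpoint places both terms under Banff, and the earlier sentence on Banff scoring does not restrict it to transplant nephropathy. Section 19.b reports the interim result as a chronic allograft nephropathy rate, and section 16 speaks of moderate to severe nephropathy; neither is a drug-attributed label. Structured grading narrows the room for bias but does not close it.

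**The result would rarely turn on this.** A reader might infer that unmasked reading can decide the trial. In the 4.5-point case the expected difference gives z = 0.045/0.0656 = 0.69, p = 0.49. Even the 10.5-point case gives z = 0.105/0.0630 = 1.67, p = 0.10. Large inflation needs large differentials, for which the documents give no evidence.

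**Changing a primary endpoint now is itself a risk.** This stands. Section 15.e records formal analyses at 60 and 140 subjects, the second published. Removing the calcineurin component would be an endpoint change made with data in hand, so it is not proposed.

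**Conclusion.** The point holds in a limited form. A judgement-based primary endpoint in a non-blinded trial has no specified protection against differential reading, and its label names the drug class under test. The exposure is confined to continuation versus withdrawal and to biopsies after month 6. Any bias would favour withdrawal.

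Its size cannot be known from the documents. Across the scenarios tried, the effect runs from negligible (5.6% false positives for 1.5 points), through about 10% for 4.5 points and 27% to 34% for 10 points, to more likely than not for 15 points. These figures rest on assumed rates, full margins of 90, and every subject in Groups 3 and 4 actually converting. Conversion is in fact conditional on no rejection and on tolerating the required sirolimus trough, so the differential across a randomised margin would be diluted. The GFR endpoint and the tacrolimus balance of the rATG comparison are not affected.

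The change is worth making because it is cheap and cannot be supplied at analysis.

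**What to change.** 1. State that the research Banff score for primary endpoint 1, and for biopsy-proven rejection, is assigned by the existing pathologist from coded slides, without group, current drugs or trough levels, at least for the 12- and 24-month surveillance biopsies.
2. Keep the research score separate from patient care: for-cause biopsies are reported clinically without delay and receive a coded research score separately.
3. State that a lesion counts toward the joint endpoint by its histological grade, whichever of the two labels it is given. Report calcineurin attribution descriptively, and do not remove the component.
4. Re-score earlier biopsies in the same way only where slides are retrievable. Section 10.g says the project banks no tissue, and the documents do not say whether clinical slides are kept.

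**Cost:** slide coding by the study coordinator and some additional time for the pathologist. No extra biopsy is needed. No extra reader is needed if one pathologist already reads these biopsies, which the protocol does not state. Section 15.e leaves the timing of the withdrawal-phase analysis open, so the change can still be put in place before that analysis is fixed.
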